### Assessment of sleep

Infant and maternal sleep will be measured with retrospective questionnaires and prospective actigraphy and sleep diaries. The extended Brief Infant Sleep Questionnaire (BISQ; 24 items) will evaluate infant bedtime problems, excessive sleepiness, awakenings, and sleep practices (e.g., bed/room-sharing, sleep position) [66, 67]. This questionnaire has been validated against sleep diaries and actigraphy [67]. To assess the mother’s sleep we will use the Pittsburgh Sleep Quality Index (PSQI), a 19-item questionnaire that measures sleep quality over the past month [68]. It has demonstrated reliability and construct validity among pregnant and postpartum mothers [69–71].

Actigraphy is a standard, valid, noninvasive measure for assessing sleep and circadian rhythm patterns across the life course [72]. We will use the Micro Motionlogger actigraph (Ambulatory Monitoring Inc., Ardsley, New York) that will be analyzed using validated sleep-wake scoring algorithms for infant sleep [73] and adult sleep [74]. The infants and mothers will wear the devices for 5 continuous days and nights after each study visit [75, 76] to capture the full development of sleep-wake patterns and circadian rhythmicity across infancy and the level of synchrony with maternal sleep-wake patterns. Primary sleep variables will be averaged across the recording period and include (1) total sleep minutes, excluding awakenings from sleep onset to final sleep bout awakening per 24 h, (2) sleep efficiency or percent of actual sleep minutes divided by the time interval from sleep onset to morning awakening per 24 h, (3) the number of long awakenings (≥5 min) during the nocturnal sleep period, (4) longest continuous sleep interval, and (5) nocturnal sleep onset time after parent-reported bedtime. Circadian rest-activity rhythmicity will be derived from cosinor analysis by which a cosine curve is applied to the data with linear regression over a specified 24 h, as well as non-parametric circadian rhythm analysis (NPCRA) to account for the presence of ultradian rhythms and to improve estimates of sleep-wake rhythmicity in newborns [77, 78]. Primary sleep-wake circadian rhythm variables from cosinor analysis with a fixed 24-h cycle will be mesor (mean activity count), magnitude (difference between mesor and peak amount of activity), acrophase (clock time of peak activity), and R^2^ (variance explained by the cosine fit or how well the data fit a 24-h circadian rhythm), and primary variables from NPCRA will be L5 (clock time of lowest activity), M10 (clock time of highest activity), amplitude (difference between L5 and M10), inter-daily stability (measure of similarity between days of rest-activity pattern; values range from 0 to 1.0 with greater values indicating greater stability), and inter-daily variability (measure of fragmentation of the rest-activity patterns) [78].

Mothers will also complete sleep diaries on the sleep of their infants and their own sleep. Diaries will be used to identify artifacts that might affect motion (e.g., swings, car seat, swaddling) and to define sleep periods from actigraphy output for infants and mothers prior to analysis with the sleep-wake algorithms [79]. Primary sleep diary variables will be (1) bed/nap clock times attempted to sleep, (2) bed/nap clock times of sleep bout awakenings, and (3) time in bed or interval between attempted bed and wake times.

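### The primary NPCRA amplitude is defined as a difference between two clock times, so as written it does not measure rhythm strength; the fragmentation index beside it is mislabelled

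*Protocol article*

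**What the plan says.** The section Assessment of sleep in the protocol article lists nine primary circadian rhythm variables: four from cosinor analysis and five from NPCRA. The first three in the NPCRA list are "L5 (clock time of lowest activity), M10 (clock time of highest activity), amplitude (difference between L5 and M10". Earlier in the same sentence the cosinor counterpart is "magnitude (difference between mesor and peak amount of activity", which is on the activity scale.

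The last two NPCRA variables are inter-daily stability, described as similarity between days, and "inter-daily variability (measure of fragmentation of the rest-activity patterns".

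Sleep efficiency, in the separate list of primary sleep variables, is "percent of actual sleep minutes divided by the time interval from sleep onset to morning awakening per 24 h". The text does not say over which window the sleep minutes in the numerator are counted.

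Statistical analyses takes the 24 h sleep and sleep-wake rhythmicity variables as the exposures of the Aim 1 time-varying effect model. Aim 3 uses sleep-wake variables again, in interaction with the gut microbiota.

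**The concern.** An amplitude should say how far activity in the active phase exceeds activity in the rest phase. A difference between two clock times says only how far apart those phases lie. A scorer who followed the published definition would carry forward a phase interval under the name of a strength measure, and a coefficient for it would be read as an effect of rhythm strength on rapid weight gain. Since the names L5 and M10 are given to times, no L5 or M10 activity level is on the list from which the intended amplitude could be rebuilt.

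The variability label raises a related problem. By its name the index is variation between days, close to the opposite of inter-daily stability. By its description it is fragmentation, which concerns switching between rest and activity within the day. The Aim 1 hypothesis under Aim and design includes greater variability of sleep-wake timing, which is a between-day idea. A reader could attach that hypothesis to an index that does not measure it.

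**Working it through.** The protocol states no figure for these variables, so there is nothing to reproduce. The check applies the definitions literally to assumed data.

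**1. Assumed inputs (not from the protocol).** Activity y(t) = 100 + A·cos(2π(t − 14)/24), in counts, with t in hours: mean 100, peak at 14:00, and A = 5, 20 or 80 for weak, moderate and strong rhythms.

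**2. Timing.** The least-active 5 h window runs from 23:30 and is centred at 02:00. The most-active 10 h window runs from 09:00 and is centred at 14:00. Neither depends on A.

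**3. Amplitude as written (time difference).** Between window midpoints: 14.0 − 2.0 = 12.0 h. Between window starts, as raw clock values: 9.0 − 23.5 = −14.5 h. Either way the result is the same for all three curves, to within a minute of grid rounding.

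**4. Amplitude as an activity contrast.** The mean over a window of h hours centred on the trough or peak is 100 ∓ A·k(h), where k(h) = sin(πh/24)/(πh/24).
- k(5) = 0.6088/0.6545 = 0.930
- k(10) = 0.9659/1.3090 = 0.738
- M10 level − L5 level = A × (0.930 + 0.738) = 1.668 × A

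| A | L5 level | M10 level | M10 − L5 (counts) | As written (midpoints) |
|---|---|---|---|---|
| 5 | 95.3 | 103.7 | 8.3 | 12.0 h |
| 20 | 81.4 | 114.8 | 33.4 | 12.0 h |
| 80 | 25.6 | 159.0 | 133.4 | 12.0 h |

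Differences are taken from unrounded values. The contrast varies by 80/5 = 16-fold, while the quantity as written does not move.

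**5. Does this depend on the cosine shape?** The figure of 12 h does. The invariance does not. If every deviation of a curve from its mean is multiplied by a constant c > 0, both windows stay where they are. The time difference is unchanged and the level difference is multiplied by c.

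**6. The variability label.** Set side by side, inter-daily stability has a name and a description that both refer to comparison between days. Inter-daily variability has a name that refers to comparison between days and a description that refers to fragmentation. Only the second pair conflicts.

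**7. Efficiency under two readings of the numerator (assumed infants).**

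| Night sleep, naps, interval | All 24 h sleep in numerator | Only sleep within the interval |
|---|---|---|
| 8 h, 6 h, 10 h | 14/10 = 140% | 8/10 = 80% |
| 9 h, 4 h, 10.5 h | 13/10.5 = 124% | 9/10.5 = 86% |
| 10 h, 2 h, 11 h | 12/11 = 109% | 10/11 = 91% |

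The readings give different exposures. The second cannot exceed 100%.

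**The case against.** The strongest reply is that this is compressed wording. The authors define the cosinor magnitude correctly in the same sentence and cite a methods source for the NPCRA variables, and standard scoring would return an activity difference whatever the article says. Nothing shows that hours will be computed. Amplitude is also only one of nine primary circadian variables. Cosinor magnitude and R² also bear on rhythm strength and are soundly defined, and no hypothesis under Aim and design names amplitude. Likewise, someone who computes what the variability parenthesis describes will obtain fragmentation despite the label.

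Most of that stands, and it limits the consequence: the main hypotheses do not hang on this variable. It does not remove the error. The text gives an explicit rule for a variable that it calls primary, and the rule yields the wrong quantity. This is a definition stated wrongly, not detail left to a fuller document.

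Two stronger readings are tempting, and the document supports neither.

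- A reader might infer that sleep efficiency as defined exceeds 100%. That needs nap minutes in the numerator, which the text does not say. The ordinary reading counts sleep within the interval, which gives 80% to 91% in the examples above. The words about 24 h come after the interval and do not settle the numerator.
- A reader might infer that clock times crossing midnight will be averaged arithmetically. The sentence "Primary sleep variables will be averaged across the recording period" governs the five listed sleep variables and names no type of mean. Only the fifth, nocturnal sleep onset after the reported bedtime, could be a clock time, and it can equally be a delay in minutes, which averages without difficulty. Acrophase, L5 and M10 come later and are not said to be averaged. Harm would need a clock-time reading, raw 0–24 coding and onsets on both sides of midnight. The coding of timing variables is detail that an article may leave to the full protocol or SAP.

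**Conclusion.** The point holds for amplitude and for the variability label. On the protocol's own definitions, NPCRA amplitude is a time difference: about 12 h for a symmetric daily rhythm, weak or strong, while the activity contrast in the assumed curves differs 16-fold. It therefore carries no information on the size of the rest-activity contrast that it is named for. The numerical illustration rests on assumed cosine curves, but the invariance to rhythm strength does not. The name inter-daily variability contradicts its own description.

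Both are probably slips of wording, and other rhythm-strength measures in the plan are unaffected. They should still be corrected before scoring, because these variables are named as primary and feed Aim 1. The sleep-efficiency numerator is an ambiguity to clear up, not an error. No finding is made on the averaging or model coding of clock times.

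**What to change.** In Assessment of sleep:

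- Define L5 and M10 as mean activity levels in the least-active 5 h and most-active 10 h, and give their timings separate names, such as L5 onset time and M10 onset time.
- Define amplitude as M10 level minus L5 level, or as that difference divided by the sum of the two levels, and state which.
- Rename the fragmentation index intra-daily variability.
- As a clarification, state that the sleep-efficiency numerator is limited to sleep minutes within the interval from sleep onset to morning awakening.

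The cost is wording and a check of the scoring settings. The activity records are already being collected, so no new data, visits or participants are needed, and the Aim 1 model keeps its form.

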### Fecal sample collection

Mothers and infants will be asked to collect fecal samples at each study timepoint using sterile swabs (HydraFlock Double Flocked Swab #25–3306-2H BT, Puritan, Guilford, ME). Maternal fecal samples will be collected by swabbing soiled toilet paper. Infant samples will be collected from soiled diapers. Date and time of collections will be recorded by the mothers. Supplies will be provided to mothers the week before planned in-home visits with instructions to collect that day’s sample from the infant’s diaper and immediately store it on ice in an insulated cooler. Study staff will pick up tubes within 24 h of collection and transport them on ice to the laboratory for storage at − 80 °C until processing.

Soiled infant diapers will be collected for additional secondary analyses including metabolomics and exfoliomics analyses (see below for details). Diapers will be kept on ice in an insulated cooler and transported to the laboratory for processing.

### Assessment of gut microbiome

Microbial genomic DNA will be extracted from fecal samples using DNeasy PowerSoil Pro DNA isolation kits and a vortex-based beadbeater, the recommended method of the NIH Human Microbiome Project and previous used by our team [80]. The hypervariable V4 region of the 16S rRNA gene will be amplified from stool samples using barcoded 806R and 515F primers [81] and 5 Prime Hot MasterMix (5 Prime, Germany) in triplicate. Quality of the amplicons and potential contamination will be checked on an agarose gel. Amplicons will be quantified using Picogreen (Invitrogen), according to the manufacturer’s protocol. A total of 200 ng of amplified DNA from each sample will be pooled and cleaned using UltraClean PCR Clean-Up Kit, and then diluted, denatured (0.2 N NaOH), and sequenced on the MiSeq platform (Illumina), as previously described [81]. Due to the limited sequence diversity among 16S rRNA gene amplicons, 10% of the PhiX control library (Illumina) made from phiX174 will be added to the run. A 7 pM aliquot of the pooled 16S rRNA gene library will be subjected to paired-end sequencing using 2 × 250 bp MiSeq Reagent Kit V2 (Illumina). Sequencing will be performed by the Genomics Core at ASU using the Illumina MiSeq and MiSeq Control Software. Pooled sequences will be de-multiplexed and quality filtered using the QIIME2 software package [82]. Sequences will be assigned to operational taxonomic units (OTU) with a 99% similarity threshold using QIIME’s uclust-based open-reference OTU picking protocol against most recent SILVA or GreenGenes reference databases. Sequences that do not match the reference database will be clustered de novo; thus, all sequences will be included in the analysis. Core diversity analyses will be performed on the OTU tables, including alpha and beta diversity as well as taxonomic summaries as provided by QIIME software.

### Intestinal exfoliated cell transcriptome assessment

Stool specimens from infant diapers will be obtained using sterile tongue depressors to allow for assessment of transcript expression in sloughed host epithelial cells. Approximately 10 g of fresh stool will be transferred to a sterile 50 ml conical tube containing 10–20 ml of DNA/RNA Shield reagent (Zymo Research Corp, Irvine, California, USA) to stabilize nucleic acids. Prior to immediate storage at − 80 °C, samples will be mixed to a homogeneous slurry by hand using a sterile conical tube pestle. Samples will be shipped on dry ice to Texas A & M University for subsequent processing and analyses as previously described [83–85].

### Fecal metabolomics analysis

Approximately 120–600 mg of stool collected from soiled infant diapers will be aliquoted and flash-frozen at − 80 °C in sterile 2 mL microcentrifuge tubes until further analysis, as previously described [86]. For fatty acid extraction, fecal metabolite samples will be extracted with chloroform:methanol (2:1, v/v) after adding an internal standard (myristic acid-d27). For aqueous extraction, metabolites will be extracted using a mixture of 80:20 (v/v) methanol:water that contains methyl succinate as the internal standard. Aqueous global profiling experiments will be performed using Agilent 7820 GC-5977 MS and Thermo Scientific Electron Orbitrap Elite Velos Pro UPLC-MS instruments. To identify peaks from the MS spectra, we will make extensive use of the robust NIST and Fiehn’s libraries for GC-MS, and HMDB metabolite library and METLIN database for LC-MS experiments. We will follow general procedures for Agilent Fiehn GC-MS Metabolomics RTL library [87, 88], with minor changes incorporated to improve detection sensitivity.

Short chain fatty acids (SCFA) will be assessed using standard MS operating procedures [89]. In brief, infant fecal samples (50 mg) will be spiked with internal standard (caproic acid-6,6,6-d3, 200 μM in H_2_O, 20 μL), and then homogenized in 20 μL sodium hydroxide solution (NaOH, 0.5 M in water) and 480 μL methanol (MeOH). Afterwards, another 400 μL MeOH will be added (pH ~ 10), and upon storage at − 20 °C for 20 min, 800 μL of supernatant will be collected. Samples will be then evaporated to dryness, reconstituted in 40 μL of methoxyamine hydrochloride in pyridine (20 mg/mL), and stored at 60 °C for 90 min. Afterward, 60 μL of N-Methyl-N-tert-butyldimethylsilyltrifluoroacetamide will be added and stored at 60 °C for 30 min. SCFAs will be detected on an Agilent 7820A GC 5977 MS system installed with a HP-5 ms fused-silica capillary column (30 m × 0.25 mm × 0.25 μm; Agilent J&W Scientific, Folsom, CA).

Targeted LC-MS/MS measurements of infant fecal bile acids will be completed [90, 91]. Fecal samples (50 mg) will be spiked with internal standards (ISs, 10 μM of LCA-D4, DCA-D4, CA-D4, GCDCA-D4, and GCA-D4), then homogenized, protein precipitated, dried, and reconstituted in 100 μL methanol/water (50:50, v/v). To assess 56 bile acids, 2 μL of each sample will be injected into an Agilent 1290 UPLC-6490 MS/MS system using negative ionization mode and a Waters XSelect HSS T3 column (2.5 μm, 2.1 × 150 mm) for chromatographic separation. To determine absolute bile acid concentrations, calibration curves will be constructed for bile acid standards in reference to corresponding ISs and concentrations calculated from peak areas and calibration curves.

### Breastmilk sample collection

Human milk samples will be collected from breastfeeding mothers at up to six of the study timepoints, depending on when breastfeeding is stopped during the first year of each infant’s life. Women will be asked to hand express or pump approximately 15 mL of milk into a 50 mL sterile conical tube and store it on ice in an insulated cooler. Within 24 h of collection, samples will be transported by study staff to the laboratory for long-term storage at − 80 °C until further processing.

### Milk microbiome assessment

To assess the microbial composition of human milk samples, microbial DNA will be extracted from samples using the Quick-DNA Fungal/Bacterial Miniprep Kit (Zymo Research Corp, Irvine, California, USA), after the milk fat is removed using an adapted centrifugation protocol and disposable inoculation loop [92]. The extraction process will follow the manufacturer-recommended protocol from Zymo Research Corp. with adjustments as previously specified [92]. Milk microbiome sequencing will be performed as written for fecal samples above, after amplifying microbial DNA using V4 primers for the 16S rRNA gene.

### Infant urine collection

A minimum of 5 mL of infant urine will be collected at each of the six study visits using BPA-free pediatric urine specimen collection bags (U-Bag, Hollister, Inc., Libertyville, Illinois, USA). Collected urine will then be transferred to 30 mL Nalgene containers and stored on ice in an insulated cooler. Within 24 h of collection, study staff will transport the samples on ice to the laboratory where they will be stored at − 80 °C.

### Endocrine disruptor exposure analysis

Urine samples will be thawed and endocrine-disrupting chemical (bisphenols, phthalates, etc.) concentrations will be assessed using high performance liquid chromatography with tandem mass spectrometry as previously described [93]. Specific gravity will be measured in all urine samples to account for differences in analyte dilution.

### Assessment of covariates

Covariates from each EMG construct (Fig. 1) will include child characteristics, maternal/family characteristics and context, feeding practices and dietary intake of infants and mothers, and home and care environmental factors/exposures. Interactions among EMG constructs also will be assessed, including maternal-child interactions and feeding interactions. An overview of the measures and their relation to ecological constructs are provided in Table 1.

**Table 1 Tab1:** Summary of study variables and measures, by Ecological Model of Growth construct

			Prepartum	Postpartum					
Ecological Construct	**Variable/Type**	**Measures/Instruments**	**Pregnancy (3rd trimester)**	**3 wk.**	**8 wk.**	**3 mo.**	**6 mo.**	**9 mo.**	**12 Mo.**
Child (Host/Agent)	Birth History	Gestational age, method of delivery, birth weight & length, day 2–5 weight & length, duration of labor, antibiotic exposure (from medical chart & reported)		✓					
	Child demographics	Sex, race/ethnicity		✓					
	Medical History	Antibiotic use, illnesses, other medications		✓	✓	✓	✓	✓	✓
	Infant Temperament	Infant Behavior Questionnaire – very short form					✓		
	Reported Sleep	Brief Infant Sleep Questionnaire and parent-reported sleep diaries (5 days each		✓	✓	✓	✓	✓	✓
	Objective Sleep	Ankle actigraphy (5 days each)		✓	✓	✓	✓	✓	✓
	Food Allergy	FDA and CDC Infant Feeding Practices study II						✓	
	Gut microbiome and metabolomics	Soiled diaper & swabs (Microbial genomic DNA and metabolites)		✓	✓	✓	✓	✓	✓
	Intestinal cell transcriptomics (exfoliomics)	Soiled diaper (Microbial genomic RNA and human intestinal cell RNA)		✓	✓	✓	✓	✓	✓
	Exposure to nutrients, environmental phenols, and phthalates *	Urine sample with urine collection bag		✓	✓	✓	✓	✓	✓
	Anthropometrics	Weight and length on standardized instruments		✓	✓	✓	✓	✓	✓
Maternal & Family	Maternal demographics	Age, education, race/ethnicity, income, nativity, length of time in U.S., occupational status, shift work status, parity, birth spacing,	✓	✓					
	Maternal pregnancy factors	Pre-pregnancy body mass index, gestational weight gain, complications, medication, antibiotic exposure, alcohol/tobacco exposure (from medical chart & reported)	✓	✓					
	Acculturation	Brief Acculturation Rating Scale for Mexican Americans		✓					
	Employment changes	Return to work timing, shift work status			✓	✓	✓	✓	✓
	Discrimination	Everyday Discrimination Scale			✓				
	Maternal distress	Edinburgh Postnatal Depression Scale; Depression Anxiety Stress Scales-21		✓	✓	✓	✓	✓	✓
	Maternal knowledge/intentions for infant feeding	Breastfeeding Attrition Prediction Tool	✓						
	Maternal sleep	Wrist actigraphy, sleep diaries, Pittsburgh Sleep Quality Index		✓	✓	✓	✓	✓	✓
	Maternal beliefs about infant sleep	Maternal Cognitions about Infant Sleep Questionnaire				✓		✓	
	Gut microbiome *	Double-tip swabs (Microbial genomic DNA)		✓	✓	✓	✓	✓	✓
	Breastmilk microbiome *	Manual or breast pump expression		✓	✓	✓	✓	✓	✓
Feeding Practices & Dietary Intake	Feeding Practices (infants)	Breastfeeding duration, exclusivity, intensity mixed feeding, formula type, etc. via FDA and CDC Infant Feeding Practices study II		✓	✓	✓	✓	✓	✓
	Dietary Intake (mothers and infants)	Introduction to solid foods and early infant feeding amount/duration via direct query & 3 self-reported dietary records (evaluated with Minnesota Nutrition Data System for Research (NDSR))		✓	✓	✓	✓	✓	✓
Environment	Home environment	Home Observation for the Measurement of the Environment Inventory (HOME)			✓		✓		✓
	Daycare environment	FDA and CDC Daycare Arrangements and Feeding Practices			✓	✓	✓	✓	✓
	Food security	USDA Household Food Security Survey		✓			✓		✓
	Tobacco exposure	Direct query			✓				
	Infant sleep environment	Brief Infant Sleep Questionnaire (e.g., bed-sharing, sleep position)		✓	✓	✓	✓	✓	✓
Maternal-Child Interactions	Maternal-child interactions	Home Observation for the Measurement of the Environment Inventory (HOME), Postpartum Bonding Questionnaire			✓		✓		✓
	Bedtime interactions	Parental Interactive Bedtime Behaviors Scale				✓		✓	
Feeding Interactions	Maternal-child feeding interactions	Infant Feeding Style Questionnaire					✓		✓

*CDC* centers for diseases control and prevention, *FDA* food and drug administration

* Measure will be collected at each visit if the participant opts into these biospecimen collections

Other child characteristics beyond infant sleep, gut microbiome/exfoliome, and anthropometrics that will be assessed will include child demographics, birth history and anthropometrics (mother-reported), medical history throughout the study period (including antibiotic exposure), infant temperament with the Infant Behavior Questionnaire - Very Short Form [94], food allergies (adapted from the Food and Drug Administration and Centers for Diseases Control and Prevention Infant Feeding Practices Study II (IFPS II)) [95], and levels of endocrine disrupters via a urine sample.

Maternal characteristics with clear associations to infant RWG or GM development will be assessed. These include pre-pregnancy BMI, gestational weight gain, parity, birth spacing, pregnancy history (e.g., route of delivery, antibiotics for group B Streptococcus), pregnancy complications, medical history and health throughout the study (including antibiotic exposure), acculturation via the Brief Acculturation Rating Scale for Mexican Americans [96] which also has been used in other Spanish speaking populations, depression via the Edinburgh Postnatal Depression Scale [97, 98], stress and anxiety via Depression Anxiety Stress Scales-21 [97, 99], infant feeding knowledge and intentions via the Breastfeeding Attrition Prediction Tool [100, 101]. Other maternal factors that remain unclear with regard to RWG will also be explored in analyses, including age, race/ethnicity, education, nativity, length of time in the U.S., employment status, shift work status, return to work timing [102], perceived discrimination via the Everyday Discrimination Scale [103], perceived parental competency via the Parental Sense of Competence Scale [104], Maternal Cognitions about Infant Sleep Questionnaire [105], and COVID-19 pandemic experiences during pregnancy and immediately postpartum with the Environmental Influences on Child Health Outcomes (ECHO) Impacts of the COVID-19 Outbreak on Pregnancy - Recall questionnaire [106].

Family characteristics and contextual factors will be assessed for associations with RWG. Included factors will be number of other household members (including children), sibling order for infant, household socioeconomic status via income and occupation, and father presence.

Feeding practices and dietary intake of infants and mothers will be evaluated via three self-reported dietary records (one weekend day and two weekdays). Mothers will complete dietary records around the time of each of the six study visits. They will be asked to report on the type, frequency and quantity of foods, beverages and supplements consumed on each day. Household comparisons will be provided with each food record to assist with estimating food portion sizes. Staff will review each record and probe for missing items (e.g., beverages, condiments, etc.). During the study visit when mothers first report solid food consumption for their infants, mothers will also be asked to complete three diet records for their infants. This will be done for two weekdays and one weekend day and will be used to define the type, quantity, and frequency of foods, beverages, and supplements being consumed by participating infants. Diet records for each mother and infant will be completed for all remaining study visits. The University of Minnesota Nutrition Data System for Research (NDSR) will be used to evaluate the nutritional composition of foods and beverages consumed by mothers and infants. Mothers will also be asked to report on breastfeeding and infant feeding practices using questions adapted from the validated questionnaires of the Food and Drug Administration and Centers for Disease Control and Prevention IFPS II [95]. In brief, mothers will report on infant dietary intake prior to solid food introduction, including breastfeeding duration and the quantity and brand of formula and/or solid foods consumed over a 24-h period. Changes in feeding practices since the last visit will be assessed including formula products containing prebiotics or probiotics to account for differential effects on the GM compared to standard formulas; solid food introduction timing, type, and amount; mode of consumption (e.g., breast, bottle, cup); and scheduled vs. on-demand feeding. Breastfeeding intensity will also be assessed at each visit [107].

Home and care environment factors that will be measured will include the Home Observation for Measurement of the Environment (HOME) Inventory [108], parent-reported daycare environment (if present) including feeding and sleep environment arrangements within the care environment, with the Daycare Arrangements and Feeding Practices [95], and familial food insecurity with the USDA Household Food Security Survey [109], household tobacco exposure [110], and infant sleep environment via the Brief Infant Sleep Questionnaire [67],

Maternal-child interactions also will be measured with the Home Observation for Measurement of the Environment (HOME) Inventory [108], as well as with the Postpartum Bonding Questionnaire [111], and the Parental Interactive Bedtime Behaviors Scale [112]. Feeding interactions will be measured with the Infant Feeding Style Questionnaire [113].

